## 2 Introduction

### 2.1 Background

#### 2.1.1 Chronic myeloid leukemia

Chronic myeloid leukemia (CML) is caused by the BCR-ABL chromosomal translocation, which results from a reciprocal translocation between the long arms of chromosomes 9 and 22. The emerging fusion protein p210BCR-ABL constitutively activates multiple oncogenic signalling pathways, leading to the expansion of immature and mature myeloid cells in bone marrow and blood. The natural course of the disease is characterized by progression from a benign, chronic phase with leucocytosis, thrombocytosis and left shifted peripheral blood to acceleration and blast crisis. The progressed phases are associated with a poor prognosis and cure at this stage can only be achieved with allogenic stem cell transplantation.

#### 2.1.2 CML treatment with tyrosine kinase inhibitors (TKI)

Conventional standard therapy of CML is the treatment with ABL-specific TKI. In a randomized comparison between imatinib and the previous standard therapy, interferon alpha (IFN) in the IRIS trial, imatinib was significantly superior to IFN, both, in terms of tolerability and efficacy (i.e., durable cytogenetic treatment response). Subsequently, second generation TKI were introduced into CML therapy in order to improve tolerability and to further increase efficacy. In two large randomized trials, nilotinib, a 20-times more potent ABL-kinase inhibitor than imatinib, showed improved early molecular response rates and less progression to accelerated phase and blast crisis. In analogy, dasatinib, which is approximately 300-times more potent than imatinib, also demonstrated improved cytogenetic remission rates after 12 months of treatment and deeper and sustained molecular remissions compared to imatinib.

#### 2.1.3 Molecular response under TKI therapy

Response to TKI therapy is monitored by cytogenetic and / or real-time quantitative PCR monitoring according to the revised criteria of the European Leukemia Net (ELN). In brief, BCR-ABL minimal residual disease (MRD) level are quantitated as a BCR-ABL level according to the international scale (IS). After 12 months of treatment, a molecular remission at the level of below or equal to 0.1% (IS) - referred to as major molecular remission (MMR) - is considered as optimal response. A deeper molecular remission (MR) - that is, <0.01% (MR^4), <0.0032% MR4.5 or less (MR^5) - indicates persistence of less CML MRD, but only limited evidence suggests that a remission depth better than MMR could be associated with improved clinical outcomes such as better progression free or overall survival. However, achieving MR^4, MR4.5 or MR^5 is clinically meaningful, because it qualifies for TKI discontinuation trials.

#### 2.1.4 TKI discontinuation in CML in deep molecular remission

Because CML stem cells are TKI-insensitive, conventional TKI treatment in CML must be indefinite in order to prevent recurrence of disease. Indeed, first imatinib discontinuation attempts in CML patients with undetectable BCR-ABL MRD, relapse occurred rapidly. However, some patients still may successfully discontinue imatinib. The first systematic prospective investigation of TKI treatment discontinuation in CML was performed by the STIM-study. 41% of the patients who discontinued imatinib with undetectable BCR-ABL MRD remained durably free of relapse for now over 4 years. These results were confirmed in the A-STIM and TWISTER studies. In the smaller TWISTER study, which used similar inclusion and relapse criteria as the STIM study, relapse rate was 53% after a median of 30-41 months. No relapses occurred after 24 months. For patients who were 2 years or longer in at least MR4.5 at the time of stopping imatinib, the relapse rate after 12 months was 36% in the A-STIM trial. However, in A-STIM the definition of relapse was less strict compared to TWISTER and STIM. Relapse in A-STIM was defined as the loss of MMR (BCR-ABL >

0.1%, IS) , whereas relapse in TWISTER and STIM was defined as any loss of MR4.5  or loss of “undetectable” BCR-ABL mRNA . **Thus, approximately 40% of the patients who discontinue TKI after MR4.5 will relapse.** MR4.5 was an essential inclusion criterion in the aforementioned TKI discontinuation studies, but only approximately 40 to 45% of all chronic phase CML patients will achieve MR4.5 after 8 to 9 years of imatinib treatment . When considering also early progressions due to resistance, this translates into a **proportion of approximately only 15% of all newly diagnosed CML patients who will eventually become durably treatment free after TKI discontinuation.**

## 2.2 Interferon alpha to improve the rate of durable TKI discontinuation

Most CML patients relapse if TKI treatment is withdrawn. Treatment modalities that would improve the proportion of patients who can successfully discontinue imatinib are currently unknown.

Until the advent of imatinib, IFN was used as standard therapy in chronic phase CML patients. In contrast to imatinib, IFN induces complete cytogenetic remissions (CCyR) in only a small minority of CML patients . IFN is also significantly less potent in the induction of molecular remissions when compared to imatinib . In contrast to TKI-induced remissions, optimal molecular responses under IFN will rarely, if ever, reach a level of deep molecular response (e.g. MR4.5) . In spite of this, successful therapy discontinuation has frequently been observed with patients in IFN-induced CCyR . In fact, a BCR-ABL/ABL ratio of below 0.045%, which would correspond approximately to BCR-ABL levels in the range of an MMR measured in the standardized international scale BCR-ABL PCR, was predictive for a very high rate of relapse free survival (RFS) after IFN therapy discontinuation . In contrast, patients lacking MR^4 or MR4.5 under TKI therapy have no reasonable chance to stay free of molecular recurrence after TKI discontinuation; consequently these patients were excluded from previous TKI discontinuation studies. Indeed, even if a sustained MR^4 / MR4.5 was reached, a molecular relapse occurs in approximately 40-60% after stopping imatinib .

Thus, there is evidence that mechanisms of remission induction and maintenance differ significantly between TKI- versus IFN-induced remissions . It was therefore rational to attempt to complement suspected different modes of action of TKI and IFN within TKI/IFN combination therapy studies . Two of these trials, which used pegylated forms of IFN together with imatinib reported a significantly improved early molecular response with the combination . A more recent trial combining nilotinib and pegIFN confirmed this result and showed high MR4.5 rates within the first year of treatment . We have previously shown that CML patients receiving an upfront imatinib/IFN combination therapy show low rates of early progression and a trend towards deepening of their molecular remission despite the absence of selective Abl-kinase inhibition .

After a median of 8-years of follow up this patient cohort presented a molecular relapse-free survival (loss of MMR) of 73% (8/11 pts.) and 84% (5/6 pts.) for patients who discontinued imatinib in MMR and MR^4/MR4.5, respectively. Ten patients discontinued IFN after a median of 4.5 years (range, 0.24 to 9.3). After a median of 2.8 years (range, 0.7-5.1) nine of them remain in ongoing treatment-free remission with MR^5 (n=6) and MR4.5 (n=3) .

Thus, IFN seems to cooperate with TKI in the induction of molecular remissions and may promote the maintenance of deep molecular remissions without further TKI treatment. The underlying mechanisms of IFN activity are not well understood, but may involve immune processes. IFN, but not TKI has been suggested to elicit anti-leukemic immune responses .

IFN-mediated control of BCR-ABL-positive MRD would explain, why successful therapy discontinuation with high MRD levels (2-3 logs higher than in the STIM trials) has only been observed in IFN patients  but never with TKI.

However, IFN toxicity can limit its applicability . To overcome this problem, better tolerable and also more efficacious pegylated IFN 2a and IFN 2b formulations were introduced. In a phase II study

pegylated IFN 2a doubled the rate of CCyR^42. When combined with imatinib, 90 µg pegylated IFN 2a weekly or 50 µg pegylated 2b were more effective in terms of inducing molecular remissions than imatinib alone. Nevertheless, within the first 12 months of combination therapy a significant proportion of the patients in these two trials discontinued IFN due to intolerance.

Tolerability may be significantly improved by lowering the doses. In the above mentioned Nilotinib / pegIFN trial, a pegIFN2a dose of 45 to 90 µg weekly was well tolerated (with 73% remaining on treatment after 12 months) and efficacious. The minimally required, effective IFN dose has never been systematically defined in CML. Our recent study showed that much lower doses of IFN than conventionally used in previous studies may be sufficient to exert IFN's beneficial effects. The duration of maintenance therapy is also not defined. In our cohort study, the median duration of IFN maintenance therapy was 54 months - longer than perhaps needed. On the other hand, in a small study on 6 patients, a median of five months of IFN maintenance was ineffective. Previous recommendations from the M.D. Anderson Cancer Center and a large European registry survey suggested that conventional IFN therapy should be continued for two to three years after obtaining a complete cytogenetic remission with IFN monotherapy. However, Hochhaus et al. have shown that not the duration of maintenance treatment, but rather the depth of remission below at least MMR achieved with IFN treatment is critical to predict relapse risk.

## **2.3 Pegylated-Proline-Interferon alpha-2b (AOP2014)**

### **2.3.1 Pharmacokinetics**

The pharmacokinetic and pharmacodynamic profile of AOP2014 has been investigated in a study in cynomolgous monkeys (4/group). In the first phase, the pharmacokinetic and pharmacodynamic profiles of AOP2014 were compared with PegIFN 2a (Pegasys®) when administered subcutaneously (30 µg/kg). In the second phase, the pharmacokinetic and pharmacodynamic profiles of AOP2014 were evaluated following intravenous (30 µg/kg) and subcutaneous (300 µg/kg) administration.

There were no treatment related clinical signs or significant changes in body weight. In Phase 1, AOP2014 exhibited a pharmacokinetic profile similar to Pegasys®. In Phase 2, intravenous administration of AOP2014 at the same dose resulted in greater serum concentration of AOP2014 from 2–96 hours in comparison to subcutaneous administration in Phase 1. Relative bioavailability of AOP2014 was calculated to be 80%. Subcutaneous administration of AOP2014 at 300 µg/kg led to even higher AOP2014 concentrations at 6 to 144 hours post dose. Relative bioavailability was 42%. In healthy adult male patients, AOP2014 reached maximal plasma concentrations (1.8 to 21.3 ng/mL) after 75 to 90 hours (tmax) when 24 to 225 µg had been applied subcutaneously (n = 4 to 5). The tmax values observed did not show any dose dependence. However, after subcutaneous administration of 270 µg maximal levels (24.8 ng/mL) were seen after 116 hours (n = 5). With subcutaneous doses of 24 to 225 µg, the elimination half-life was determined as 61 to 92 hours with no obvious dose dependence (n = 4 to 5). However, after a subcutaneous dose of 270 µg the elimination half-life was 118 hours (n = 5).

The prolonged plasma half-life and the resulting increase in AUC is hoped to result in an improved therapeutic window of peg-IFN-alpha-2b.

### 2.3.2 Clinical experience with AOP2014

The Phase I/II study of AOP2014 in PV is currently ongoing (completed recruitment of 51 patients and collecting follow-up information on efficacy and safety). The AOP2014 formulation with the strength 0.18 mg/ml is being used in this phase I/II study. The maximum tolerated dose (MTD), long term safety and efficacy of AOP2014, administered subcutaneously every 14 days, are the main objectives of the study. Patients with confirmed PV diagnosis, age equal or older than 18 years, both naïve and cytoreduction pre-treated were eligible. After establishing the MTD, an extended cohort of 25 additional patients was planned to be recruited.

European LeukemiaNet criteria were used for response assessment. Interim analysis of efficacy and safety data was presented at the last, 2012 ASH annual meeting (Gisslinger et al, 2012, oral presentation and abstract). 34 patients were included into this analysis, 25 in Phase I (dose-finding) and 9 in the Phase II (cohort extension).

Median time from diagnosis was 24 months (range 0–180). 12 patients (35%) had been pre-treated with HU (mean past duration of HU pre-treatment 39 months, mean daily HU dose 950 mg). Median number of phlebotomies in the past 3 months prior to inclusion was 1 (range 0–8), a total of 21 patients (62%) were regularly phlebotomized at least once in three months prior to study entry. 11 patients (32%) had a history of thrombotic complications. Median Hct at baseline was 42% (range 36–51). Median WBC and platelet counts were  $10.6 \times 10^9/l$  (range 3.9–20.4) and  $452 \times 10^9/l$  (range 141–1019), respectively. 17 patients (50%) had splenomegaly at baseline. The median reported treatment duration was 41 weeks (range: 1 day – 80 weeks), 11 patients completed 1 year on treatment. Doses from 50 to 540 µg every two weeks were tested, the highest tested dose, *i.e.* 540 µg was determined as MTD since no DLTs occurred in the study. The mean administered dose (both Phase I and II patients) was 287 µg. After 28 weeks of treatment (21 evaluable patients), 71% of patients had hematological response (7 CR, 33%; 8 PR, 38%), at week 36 (19 evaluable patients) 8 patients (42%) achieved a CR and 8 patients (42%) a PR, overall response rate (ORR, CR+PR) was 84%. At week 52 (1 year; 11 evaluable patients), 5 patients (46%) had CR and 5 (46%) PR, ORR was 91%; 8 (73%) patients presented with completely normalized blood values, all evaluable patients did not require phlebotomy at this time point. 4 patients (of 12 evaluable for this measurement, 33%) still had an enlarged spleen at week 52. At week 76, 2 evaluable patients were complete responders. At week 52, 1 patient (of 9 evaluable, 11%) developed partial molecular response, at week 68 3 patients (of 7 evaluable, 43%) had partial molecular response. One patient with allelic burden of 22% at baseline developed complete molecular response at week 36 (still ongoing). Mainly grade 1 and 2 adverse events were reported. A total of 358 adverse events occurred. 27 patients (79%) suffered from drug-related adverse events. 9 patients (26%) developed serious adverse events; 4 SAEs were considered to be treatment related. 5 patients (15%) discontinued their study participation prematurely, 3 of them due to adverse events (deterioration of underlying disease and two cases of depression). Acceptable tolerability and sustained clinical benefits have been demonstrated in PV patients measured as overall response rate of above 90% with CRs of 46% at one year after treatment start. Most of the patients did not require phlebotomy and their hematological parameters fell with the normal range.

Based on these results the phase III randomized study PROUD-PV has previously been initiated. The aim of the study is to provide confirmatory evidence that AOP2014 is non-inferiority to HU, as measured by normalization of blood parameters and spleen size. If this aim is achieved, the study will be used as a pivotal, registration study to apply for marketing authorization of AOP2014 in patients with PV. Afterwards there was performed the CONTINUATION-PV and PEN-PV study. CONTINUATION-PV Study is an open-label, Phase IIIb extension study assessing the long-term efficacy and safety of AOP2014 in PV patients who completed the AOP2014 arm of the PROUD-PV Study in comparison to patients who completed the HU arm of PROUD-PV Study and are managed according to standard of care/best available treatment.

PEN-PV Study is an open-label, single-arm Phase III study to assess the self-administration of AOP2014 using the pre-filled pen intended for commercial use in 36 patients with PV.

In 2011, orphan designation for Ropeginterferon alfa-2b (AOP2014) for the treatment of PV was granted to AOP by the European Commission.

## **2.4 Rationale for the study**

Current standard therapy in CML is indefinite TKI treatment. This is frequently associated with side effects, unknown long-term toxicities and also significant costs. There is currently no known treatment modality, which improves the proportion of patients who can successfully discontinue TKI therapy.

1. There is a significant medical need to identify treatment concepts in CML, which enable a discontinuation of an otherwise life-long therapy (with TKI). As eluted in section 2, mounting evidence suggests that a pegylated formulation of IFN could be such a substance. It exerts a substantial synergism with TKI and also has the potential to induce a durable TFR, when applied sequentially after upfront TKI therapy. Based on this rationale, the primary aim of this study will be to increase the proportion of patients, who can permanently discontinue TKI treatment using temporary AOP2014 maintenance therapy, which will be started after stopping the TKI. Obviously, only TFR is of maximum value to patients, because it will avoid any chronic side effects and long-term toxicities of TKI, and significant annual costs (approx. 30-50.000 €).
2. There is currently no other established or experimental treatment, which has been shown to increase the rate of sustained deep molecular remissions after TKI discontinuation in CML (see 2.3). This makes this study unique.
3. The study will provide unprecedented biological insights into the effects of AOP2014 in controlling minimal residual stem cell disease induced by long-term prior TKI therapy. It will also enable to better understand mechanism of immune responses induced by IFN to control CML.
4. If the study would be positive, the findings could become treatment-changing for patients in deep molecular remission under TKI and willing to tolerate a temporary additional treatment.

## **2.5 Risk benefit assessment**

Patients, who will enter this study, will benefit from a 50% chance to durably discontinue TKI therapy. TKI discontinuation itself is very safe. There is no risk of disease progression after TKI stop and no risk of failure to regain deep molecular remission, in the event of MMR loss. Restarting with the previous TKI will essentially always restore deep molecular remission. This evidence is based on large clinical study cohorts of more than 1.000 documented patients.

Secondly, IFN was the previous standard drug in CML. It is a safe drug and, as eluted in 2.2 and 2.4 has previously been shown - in uncontrolled studies - to enable induction of a durable TFR. It offers therefore a reasonable chance to increase the overall rate of TFR in CML patients.

Due to the longstanding experience with the therapeutic use of human IFN in the treatment of diverse malignancies (melanoma, lymphoma, CML) and infectious diseases (hepatitis C) IFN can be considered as a safe drug. Potential toxicities and side effects are well predictable and consist mainly of temporary flu-like symptoms. However, rarely, there are also significant side effects such as induction of auto-immune diseases (thyroiditis, vitiligo, sarcoidosis etc.). Hair loss, psychiatric symptoms and other auto-immune symptoms may also occur. All side effects can usually be controlled by dose reductions or treatment discontinuation. Toxicities require extremely rarely active treatment intervention.

This altogether suggests that benefits associated with a durable TKI discontinuation induced by AOP2014 by far outweigh potential risks associated with AOP2014 treatment. Any indication that AOP2014 maintenance, will negatively affect relapse rates or progression after TKI discontinuation cannot be identified, further underscoring the positive benefit/risk ratio.

### **3 Study Objectives**

The purpose of the study is to evaluate the efficacy and safety of pegylated-proline-interferon alpha-2b (AOP2014) administered biweekly for a maximum of 15 months in patients with chronic phase of CML, who discontinued TKI treatment with a residual BCR-ABL mRNA level of at least MR^4.

#### **3.1 Primary objective**

The primary objective of this study will be to evaluate the efficacy of AOP2014 administered bi-weekly subcutaneously (s.c.) in preventing molecular relapse (loss of MMR) in CML patients, who discontinue ABL tyrosine kinase inhibitor therapy (TKI) in deep molecular remission of MR^4 or better (MR4.5, or MR^5).

#### **3.2 Secondary objectives**

- To assess tolerability and toxicity of AOP2014.
- To assess quality of life before and after TKI discontinuation.
- To evaluate the safety of maintenance therapy with AOP2014
- To assess overall survival.
- To explore the value of 95 CD86+pDC / 10^5 lymphocytes at baseline in predicting risk of molecular relapse (loss of MMR)
- Carry out immunological and genetic biomarker studies to study biology of TFR, and identify predictors IFN response (e.g. by mRNA sequencing of whole blood or leukocyte subpopulations, PD-L1-, PD1-, CD62L- measurements by FACS, T-cell activation and exhaustion marker measurements)

All patients are eligible to continue observation in the Post-Study Follow-up phase.

#### **3.3 Post Study Follow Up (PSFU) Objectives**

- Documentation of durability of rate of TFR and RFS (BCR-ABL molecular remission status according to IS)
- Assessment of overall survival (OS)
- Descriptive: type of current treatment for CML, if TFR was lost (demographic data including treatment history)

## 4 Study Endpoints

### 4.1 Primary endpoint

The primary efficacy endpoint is molecular relapse free survival, RFS 7 months after randomization.

Relapse is defined as loss of major molecular remission, MMR, which is any increase of the BCR-ABL ratio to  $> 0.1\%$  according to the international scale (IS). Time to relapse is defined as the time from randomization to relapse.

### 4.2 Secondary endpoints

- RFS 13 months after randomization
- RFS 25 months after randomization
- Safety, tolerability and toxicity based on incidences of adverse events, serious adverse events, frequency of clinical laboratory tests by worst toxicity grade
- Quality of life (EORTC QLQ-C30 and EORTC-QLQ-CML24 questionnaires) The QoL assessment in this study is planned to gain information on the QoL of CML patients under stopping conditions. The data will be compared between the treatment groups and to QoL of normal population. Furthermore, results of the CML24 module should be shared with the EORTC group to complete the validation of this questionnaire
- Explore the value of  $95 \text{ CD86+ pDC} / 10^5$  lymphocytes at baseline (before TKI stop) as a predictor of TFR
- Overall survival (OS), defined as the time between the date of randomization and the date of death from any cause.
- Explore immunological and genetic biomarkers to study biology of TFR, and identify predictors IFN response (e.g. mRNA sequencing of whole blood or leukocyte subpopulations, PD-L1-, PD1-, CD62L- measurements by FACS on peripheral blood subsets, T-cell activation and exhaustion marker measurements, PR1-CTL assessment and cytokines).
- Evaluation of cytokines/chemokines (i.e., IL-6, IFN- $\alpha$ , IL 10, and others).
- Kinetics of BCR-ABL transcript level over time after TKI stop

## 5 Post study Follow Up endpoints

- Molecular relapse-free survival 36, 48 and 60 months after randomization for patients in arm A and B, who were in TFR at the end of month 25.

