9. **PSFU:** Patients, who are in TFR 25 months after randomization, are recommended to undergo quantitative BCR-ABL RT-PCR (IS) monitoring every three months. However, an "off study" documentation of molecular remission will be required only once yearly for three years, namely 36, 48 and 60 months after randomization.  
For all patients, the following data will be documented in PSFU:
  - a) Survival (y/n)
  - b) Type of current treatment for CML
  - c) Demographic data including treatment history and relevant medical history (secondary malignancies, cardiac disease, auto-immune disease, progression of CML)
  - d) BCR-ABL RT-PCR (IS)

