#### **12.1.7 Post Study Follow Up (PSFU)**

Patients, who are in TFR 25 months after randomization, are recommended to undergo quantitative BCR-ABL RT-PCR (IS) monitoring every three months. However, an “off study” documentation of molecular remission will be required only once yearly for three years, namely 36, 48 and 60 months after randomization (see study flow chart 1.1 and Table 1 and Table 2). For all patients, the following data will be documented in PFSU 36, 48 and 60 months after randomization:

- a) Survival (y/n)
- b) Type of current treatment for CML
- c) Demographic data including treatment history and relevant medical history (secondary malignancies, cardiac disease, auto-immune disease, progression of CML)
- d) BCR-ABL RT-PCR (IS)

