### 16.4 Efficacy Variables

The primary efficacy endpoint is molecular relapse-free survival (RFS).

Time to relapse is defined as the time from randomization to relapse (loss of MMR = increase of BCR-ABL ratio to  $> 0.1\%$  according to the IS) or to death from any cause. Survivors without relapse will be censored on the last date they were known to be alive.

The secondary efficacy endpoints are:

- Treatment outcome correlation with predefined biomarkers ( $>$  or  $<$  95 CD86+pDC before TKI discontinuation, PD-1L, PD1 expression, PR1-CTL and cytokines in peripheral blood measured at date of randomization and at designated time point thereafter).
- Overall survival is defined as time from randomization to death from any cause. Survivors will be censored on the last date they were known to be alive.
- The QoL assessment in this study is planned to gain information on the QoL of CML patients under stopping conditions. The data will be compared between the treatment groups and to QoL of normal population. Furthermore, results of the CML24 Module should be shared with the EORTC group to complete the validation of this questionnaire.

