## 16.9 Analyses of “off study follow-up”

Molecular relapse-free survival (RFS) will be reported at the three fixed times, 36, 48, and 60 months after randomization. Again, at the final post study follow-up analysis, molecular RFS will also be analysed as a time-to-event variable.

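### The post-study RFS endpoint at 36, 48 and 60 months is fixed in a subset chosen by the trial's own outcome, so arm figures in that subset are not a randomized comparison

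*Protocol*

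**What the plan says.** Protocol section 5 places RFS at 36, 48 and 60 months at the head of the post-study endpoints and limits it to a subset: "for patients in arm A and B, who were in TFR at the end of month 25". The clock starts at randomization. Section 16.4 says "Time to relapse is defined as the time from randomization to relapse", and section 5 counts its three times from the same date.

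Section 16.9 states that RFS "will be reported at the three fixed times, 36, 48, and 60 months after randomization" and that, at the final post-study analysis, "molecular RFS will also be analysed as a time-to-event variable". It names no population for either, so it neither repeats nor lifts the restriction. The intention-to-treat rule in section 16.7 is written for the primary and secondary efficacy endpoints and does not mention the post-study endpoint.

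The post-study objective in section 3.3 is "Documentation of durability of rate of TFR and RFS". Collection is not restricted. Section 12.1.7 says "For all patients, the following data will be documented in PFSU 36, 48 and 60 months after randomization", and BCR-ABL is on the list that follows. Section 16.11 makes everything beyond the four hypotheses explorative.

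**The concern.** A patient enters the section 5 analysis only by still being in TFR at month 25. RFS at month 25 is itself the subject of confirmatory hypothesis 4, so the subset is selected by an outcome the treatment is intended to alter. If the drug works, the two subsets differ in size and in the kind of patient they hold, and randomization no longer makes them comparable.

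The design gives this practical weight. Under section 8.2.4, a patient in arm A at month 25 has been off AOP2014 for 10 months, while a patient in arm B has been off all therapy for 24. The same section cites a discontinuation study in which few relapses came late after stopping TKI. If AOP2014 postpones some relapses rather than preventing them, those relapses could fall after month 25 in arm A, while their counterparts in arm B were removed before the analysis began. Telling delay from prevention is a main use of long follow-up, and an estimate confined to month-25 survivors in TFR cannot do it by comparing arms.

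There is also a reporting risk. One analyst could follow section 5 and another could read section 16.9 as covering all randomized patients. They would publish quite different percentages under the same label.

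**Working it through.** **Inputs.** Section 16.10 gives RFS in arm B of 55%, 50% and 45% at 7, 13 and 25 months, 20 points more in arm A at each time, 192 evaluable patients (96 per arm) and 214 randomized (107 per arm). The protocol gives no RFS beyond month 25, so every later loss below is an assumption. For the arithmetic, being in TFR at month 25 is taken as being relapse-free at month 25.

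**The plan's own figures.** For 45% vs 65%, two-sided 0.05, power 80%, uncorrected chi-square, n per arm = [1.960 × √(2 × 0.55 × 0.45) + 0.842 × √(0.45 × 0.55 + 0.65 × 0.35)]² / 0.20² = 96 after rounding up. This gives 192, and 192 / 0.9 = 214 after rounding up. Power with 96 per arm is 83.3% at 7 months, 81.3% at 13 and 80.0% at 25. The stated design reproduces.

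**Size of the subset.** Of 96 evaluable per arm: 96 × 0.65 = 62 in arm A and 96 × 0.45 = 43 in arm B. Of 107 randomized per arm: 70 and 48.

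**The two estimates.** Let a and b be the percentage points of RFS lost between months 25 and 60 in arms A and B.

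- All randomized: (65 − a) vs (45 − b), difference 20 − a + b.
- Month-25 subset: (65 − a)/65 vs (45 − b)/45.

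| Assumed loss A / B (points) | All randomized A vs B | Difference | Subset A vs B | Difference |
|---|---|---|---|---|
| 5 / 5 | 60% vs 40% | +20.0 | 92.3% vs 88.9% | +3.4 |
| 10 / 5 | 55% vs 40% | +15.0 | 84.6% vs 88.9% | −4.3 |
| 10 / 3 | 55% vs 42% | +13.0 | 84.6% vs 93.3% | −8.7 |
| 15 / 3 | 50% vs 42% | +8.0 | 76.9% vs 93.3% | −16.4 |

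The 5 / 5 row takes the loss that section 16.10 implies in each arm from month 13 to 25 (70% to 65% and 50% to 45%) and applies it once over months 25 to 60.

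**Equal losses.** With a = b = d, the subset difference is d × 100 × (1/45 − 1/65) = 0.684 × d points: 2.1 for d = 3, 3.4 for d = 5 and 6.8 for d = 10. The randomized difference is 20 throughout.

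**When the sign reverses.** The subset favours arm B when a/65 > b/45, that is a > (65/45) × b = 1.44 × b. All randomized patients still favour arm A when a < b + 20. The two disagree in direction only when both conditions hold.

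**The case against.** The case on the other side has four parts, and much of it stands.

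- **No contrast is specified.** Section 5 names no between-arm test for this RFS endpoint. Section 5.1 does speak of comparison, but for overall survival and for demographic and history data. The objective is durability, and section 8.2.5 calls the phase purely observational. Durability among patients still in TFR is a legitimate conditional quantity. This stands, and the fix keeps that figure. Section 5 does not, however, label it as conditional, and it names both arms on a clock that starts at randomization, which invites the contrast.
- **The randomized comparison is intact.** A reader might infer that the plan gives up the randomized comparison. It does not. The tests at 7, 13 and 25 months and the log-rank test are made in the intention-to-treat population, and none is touched.
- **There is no contradiction.** A reader might infer that sections 5 and 16.9 define different endpoints. Section 16.9 is silent on population. It may inherit the restriction, or its time-to-event sentence may point back to the analysis of all randomized patients. The text does not settle which. That is an ambiguity to close, not a conflict.
- **Reversal is not predicted.** A reader might infer that the subset figure will turn against arm A. Nothing in the protocol forecasts the late relapse that this needs, and equal 5-point losses leave arm A ahead in the subset.

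It may also be said that the population of an explorative summary can wait for the statistical analysis plan. Here the protocol has already fixed one, so the point concerns a stated definition rather than an omission.

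**Conclusion.** The point holds as a badly fixed population for an explorative endpoint. The section 5 estimate describes durability within each arm and cannot carry a treatment comparison. The supportable consequence is a different and usually much smaller difference between arms: with equal 5-point losses, +3.4 points in the subset against +20 in all randomized patients. Reversal is a possibility confined to the stated range, for example −4.3 against +15 with losses of 10 and 5 points. It is plausible because the arms differ in time off therapy at month 25, but it is not a forecast.

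These sizes rest on the protocol's 65% vs 45% and on assumed later losses. They also equate TFR with being relapse-free. In practice a patient who restarts TKI without loss of MMR leaves TFR without a relapse, so the section 5 restriction removes some such patients as well. The four confirmatory tests and the sample size are unaffected.

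**What to change.** In sections 5 and 16.9, define RFS at 36, 48 and 60 months, and the post-study time-to-event analysis, in all randomized patients as randomized. Count relapses before month 25 as events, including in patients whose later BCR-ABL values are again in MMR after resuming TKI. Name the population in both sections so that they agree.

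Keep the month-25 TFR subset as a supplement. Label it as conditional on TFR at month 25, present it as a within-arm description of durability with its denominators, and state that arm differences in it are not a treatment effect.

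Relapses up to month 25 are recorded in the main study and post-study BCR-ABL is documented for all patients. The cost is a change of wording and a small amount of extra analysis, with no new data and no change in sample size.
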